### Handling of data

Two members of the research team will perform study monitoring. Remote monitoring will be performed to signal early aberrant patterns, issues with consistency, credibility, and other anomalies. Patient data will be collected in pseudonymous form using a patient (identification) number composed of three digits corresponding to the patient inclusion number. Study data will be collected and managed using an investigator-initiated trial EDC (IIT-EDC) tools. IIT-EDC is a password-protected, intranet-based application designed to support data records for research studies (website: http://10.15.7.137). Full access to the final trial dataset will be granted to selected investigators. All original records, including consent forms, reports of suspected unexpected serious adverse events (SAE), and relevant correspondences, will be archived at the trial sites for 10 years. The clean trial database file will be anonymized and maintained for 10 years.

### Plans for communicating important protocol amendments to relevant parties (e.g., trial participants and ethical committees)

A “substantial amendment” is defined as an amendment to the protocol or any other supporting documentation that is likely to affect to a significant degree one or more of the following: the safety or physical or mental integrity of the subjects of the trial; the scientific value of the trial; the conduct or management of the trial; or the quality or safety of any intervention used in the trial.

All substantial amendments will be notified to the Institutional Review Board of Zhongshan Hospital Fudan University (China) and to the competent authorities. Non-substantial amendments will be recorded and filed. In the case that amendments concern or affect participants in any way, they will be informed about the changes. If required, additional consent will be requested and registered. In addition, the online trial registry will be updated accordingly.

### Safety

All adverse events (AE) thought to be related to the trial will be reported to the trial coordinating center. According to local laws and regulations, the participants may receive free treatment provided by our unit or be compensated if any injury related to this study does occur, and all suspected unexpected SAEs will be reported to the data monitoring and safety committee (DMSC). The DMSC is independent of the trial investigators and will perform an ongoing review of safety parameters and overall study conduct. The DMSC comprises two independent experts in large-scale clinical trials and one independent statistician.

The DMSC will be responsible for safeguarding the interests of the trial participants, assessing the safety and efficacy of the interventions during the trial, and monitoring the overall conduct of the clinical trial. To enhance the integrity of the trial, the DMSC may also formulate recommendations relating to the recruitment/retention of participants, their management, improving adherence to protocol-specified regimens and retention of participants, and procedures for data management and quality control.

### Statistical analysis

#### Sample size

The incidence of severe gas embolism in the right ventricular system detected by TEE will be used as the primary outcome parameter. Based on results from preliminary trial, the incidence of grade 3 and above gas embolism in LLR using low and standard intra-abdominal pressure was 45% and 69%, respectively. Sample size was calculated by a web-based calculator (http://powerandsamplesize.com/Calculators/). For the power of 80% and a level of significance of 5% against the two-sided alternative hypothesis, 126 participants are required to detect the observed difference in gas embolism incidence using chi-square test. Expecting 10% drop-out of participants, a sample size of 140 is required.

#### Analysis

Continuous distribution of the data was assessed by visual inspection of histograms and D’Agostino–Pearson’s normality tests. For both arms, the baseline characteristics will be expressed as counts and percentages, means and standard deviations, or medians and interquartile ranges, as appropriate.

Ventilatory parameters and vital signs during the surgery will be analyzed using a mixed-effect model with repeated measures, and with patients as a random effect. No or minimal losses to follow-up for the primary and secondary outcomes are anticipated. The intention-to-treat (ITT, all randomly assigned cases) population is used for all outcomes analysis. The supportive analysis is based on a full analysis set (FAS, all randomly assigned patients who received corresponding PP until liver resection). However, if more than 1% of missing data are found for the primary outcome, a sensitivity analysis using multiple imputations and estimating equation methods will be carried out.

Hypothesis tests will be two-sided with a significance level of 5%, with the exception of the primary outcome.

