### Randomization and blinding

Randomization will be conducted over a dedicated, password-protected, SSL-encrypted website (edc.fudan.edu.cn) to allow immediate and concealed allocation. Each patient will be given a patient number and randomization number. The allocation sequence, with an allocation ratio of 1:1 for each group, will be generated using a minimization algorithm stratified according to risk of intraoperative exposure of the hepatic vein, liver cirrhosis status, and history of abdominal surgery. Participant allocation will be performed by a specific local investigator; the investigator will log into the randomization system using a personal ID code and will enter any relevant information. This will ensure that the patient receives only surgery under the randomized PP. The process of sequence generation and storage will be managed by an independent database manager who is not involved in patient care.

Surgeons and assessors of intraoperative gas embolism grades and PQRS [21] will be blinded to the treatment allocation. At least two assessors will be involved in the study. One assessor will determine the intraoperative gas embolism grades, and the second assessor will perform postoperative visits and assessments of the primary and secondary endpoints. All patients will be followed up by researchers who are blinded to the intraoperative grouping, and each patient will be evaluated by the same researcher during the perioperative period.

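### As named, the sensitivity analyses for a missing primary outcome do not test departures from missing-at-random, and the protocol disagrees with itself on how much loss to expect and what happens to patients without the outcome

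*Protocol article*

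**What the plan says.** All references are to the protocol article.

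- **Remedy for missing outcomes (Analysis).** Above a threshold of 1% missing for the primary outcome, "a sensitivity analysis using multiple imputations and estimating equation methods will be carried out". No missingness assumption, imputation model or type of estimating equation is given.
- **Expected loss, first statement (Sample size).** "Expecting 10% drop-out of participants, a sample size of 140 is required".
- **Expected loss, second statement (Analysis).** "No or minimal losses to follow-up for the primary and secondary outcomes are anticipated".
- **Who is analysed (Analysis).** The intention-to-treat set, meaning every randomised patient, is used for all outcomes.
- **Patients with too much missing (Study dropouts).** They are replaced by new patients, and missing measurements that feed the primary outcome are given as one example. Patients converted to open surgery leave the study, but their data up to conversion are analysed.
- **The outcome and its test (Outcomes; Primary outcome).** Each patient contributes one binary result, embolism of grade 3 or more at any time during the resection, read by TEE. The arms are compared by risk ratio and chi-square test, and no covariates are mentioned.

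**The concern.** A sensitivity analysis for missing data is useful when it changes the assumption most open to doubt. Here that assumption is that, given the observed data, patients without a reading have the same embolism risk as those with one. Ordinary multiple imputation keeps that assumption. Unweighted estimating equations use the same complete cases as the main test, and with one binary result per patient there are no repeated measurements for them to exploit. Agreement among the three analyses would say little about informative loss.

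Informative loss is conceivable. Conversion to open surgery ends the laparoscopic observation period because of what is found at operation. Whether that is linked to embolism is an inference, not something the article states.

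The handling rules add to the problem. If patients without the outcome are replaced, they may drop out of the very analysis meant to examine them, and the analysed set is no longer everyone randomised. At stake is how far a reader can trust a statement that the primary result is robust to missing data.

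**Working it through.** **Inputs from the protocol article**

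- Two-sided 5% level (Sample size: "a level of significance of 5% against the two-sided alternative hypothesis") and 80% power.
- Event rates: "using low and standard intra-abdominal pressure was 45% and 69%, respectively" (Sample size).
- Allocation 1:1 (Randomization and blinding).
- Evaluable patients: "126 participants are required to detect the observed difference in gas embolism incidence using chi-square test" (Sample size), so 63 per arm.
- Total 140 after a 10% allowance, so 140 − 126 = 14 patients.

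**Step 1. Reproduce the plan's figures.** The unpooled two-proportion formula is

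n per arm = (1.960 + 0.842)² × [0.45×0.55 + 0.69×0.31] / (0.69 − 0.45)² = 7.849 × 0.4614 / 0.0576 = 62.9, rounded up to 63.

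That gives 126 in total, and 126/0.9 = 140. Both stated figures reproduce. The 1% trigger is met at 2 missing of 140 (1 of 140 is 0.7%).

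**Step 2. Complete cases.** Assumptions of this check, not of the document: 14 outcomes missing, split 7 and 7, and observed rates close to plan. 63 × 0.45 = 28.4 and 63 × 0.69 = 43.5, taken as 28/63 and 43/63.

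Pearson z = (43 − 28)/63 / √[0.5635 × 0.4365 × 2/63] = 0.2381/0.0884 = 2.69, p = 0.007. Risk ratio 0.65 (95% CI 0.47 to 0.90).

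**Step 3. Fill in the missing results.** Let i and j be the events among the 7 missing low-pressure and 7 missing standard-pressure patients. The data become (28+i)/70 vs (43+j)/70, with 8 × 8 = 64 combinations.

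| Fill-in | Low vs standard | Risk ratio | p |
|---|---|---|---|
| Best case for low pressure (i=0, j=7) | 28/70 vs 50/70 | 0.56 | 0.0002 |
| About the planning rate in each arm (i=3, j=5) | 31/70 vs 48/70 | 0.65 | 0.004 |
| All missing are events | 35/70 vs 50/70 | 0.70 | 0.009 |
| All missing are non-events | 28/70 vs 43/70 | 0.65 | 0.011 |
| Worst case for low pressure (i=7, j=0) | 35/70 vs 43/70 | 0.81 (0.60 to 1.10) | 0.17 |

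The planning-rate row is a single fill-in, so its p-value overstates precision.

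**Step 4. Tipping point.** The result depends almost entirely on i − j. At i − j = 3, p is 0.040 to 0.042. At i − j = 4, p is 0.060 to 0.062. Combinations with i − j ≥ 4 number 4 + 3 + 2 + 1 = 10, so significance is kept in 54 of 64.

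**Step 5. How extreme that is.** The 64 combinations are not equally likely. If the missing patients in both arms had the same 57% risk, the midpoint of 45% and 69%, i − j ≥ 4 would occur in 2.7% of trials (two independent binomials of size 7).

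**Step 6. False-positive rate under no true effect (57% in both arms, 63 evaluable per arm, exact enumeration of the chi-square test).**

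- Loss unrelated to outcome: 5.8%. This is the baseline, not 5%.
- The 10% lost from the low arm all events, so the observed rate is (0.57 − 0.10)/0.90 = 0.522 vs 0.570: 9.5%.
- In addition, the 10% lost from the standard arm all non-events, so its observed rate is 0.57/0.90 = 0.633: 26%.

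The last two are extremes, not forecasts.

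**Step 7. The passages side by side.** Inflating from 126 to 140 protects power only against patients who lack the primary outcome, so the allowance in Sample size implies up to 14 such patients. Analysis says few or none. Study dropouts would replace at least some of them, in which case the inflation would partly duplicate the replacement. The three statements cannot all describe the same trial.

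**The case against.** The strongest reply has four parts.

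1. **The method names leave room.** Multiple imputation is a framework and can be delta-adjusted; estimating equations can be weighted. The imputation model is commonly left to a statistical analysis plan, which is not shown. This stands. It limits the point to the methods in their usual form, and it rules out saying that the planned analyses cannot reveal a problem.

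2. **The assumptions are not identical.** A reader might infer that the sensitivity analyses rest on the same assumption as the main analysis and must agree with it. The document does not support that: it states no missingness assumption. An unadjusted complete-case test needs missingness unrelated to outcome within arm, while imputation with covariates needs this only conditionally. Nor is imputation confined to baseline variables. Study visits and data collection lists end-tidal CO2, blood pressure, cerebral oxygen, vasoactive infusions, blood loss and duration of surgery. This also stands.

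3. **The 10% is an allowance.** A reader might take it as a forecast of 14 missing primary outcomes. The outcome is read in theatre, so later loss to follow-up does not remove it, data before conversion are kept, and an embolism graded before the operation changes course is already recorded. The reply is right that 14 is an upper working figure. It does not remove the conflict between the two statements on loss.

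4. **Reversal needs strongly one-sided loss.** True, as steps 4 and 5 show.

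What survives is that the article commits to specific methods, names none that departs from missing-at-random, and gives inconsistent rules for patients without the outcome.

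**Conclusion.** The point holds in this limited form and should be acted on before unblinding. In their usual form the named methods leave informative loss untested, and the estimating-equation analysis, if unweighted, adds little to the complete-case result. Separately, Study dropouts, Sample size and Analysis need to be reconciled; that part rests on the text alone.

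The numerical size rests on three assumptions: 14 missing outcomes, an even 7/7 split, and observed rates equal to the planning rates. If all 14 were in one arm, the worst case would be p=0.12 (all in low pressure) or p=0.18 (all in standard pressure). With fewer missing the risk shrinks quickly: one per arm, filled in against low pressure (32/70 vs 47/70), gives p=0.011.

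It would be wrong to conclude that the expected loss is likely to overturn the trial. A loss of that size could do so only under markedly differential missingness against low pressure.

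**What to change.** 1. Keep multiple imputation and label it the missing-at-random analysis. Include the three stratification factors and the intraoperative data already collected in the imputation model.
2. Drop the estimating-equation analysis, or specify it as weighted and say what the weights model.
3. Add a tipping-point (delta-adjusted) table of missing events by arm, with best-case and worst-case bounds, and state beforehand that robustness will be judged by whether the tipping point is clinically plausible.
4. Keep randomised patients without the outcome in the intention-to-treat denominator for these analyses, even if additional patients are enrolled.
5. Make Study dropouts, Sample size and Analysis give one expected loss for the primary outcome and one rule for patients who lack it.

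The cost is revised wording and one extra table, with no new data and no change to the primary test. The possible downside is a less favourable robustness statement.

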#### Primary outcome

The effects of the intervention on the incidence of severe gas embolism in the right ventricular system detected by TEE will be reported as numbers and percentages estimated with risk ratios and 95% confidence intervals (CI), as calculated by Wald’s likelihood ratio approximation test and with *χ*^2^ tests for hypothesis testing.

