At randomization (stratification): risk of intraoperative exposure of hepatic vein Y/N, liver cirrhosis status Y/N, and history of abdominal surgery Y/N.

During the surgical procedure, the TEE probe will be placed through the esophagus until extubation, and the following data will be collected:
Anesthetic data: type and doses of hypnotics, opioids, and muscle relaxants; duration of anesthesia; total volume of maintenance fluid; total number of blood products; ventilator settings (VT, respiratory rate, PEEP, FiO_2_); baseline (and then hourly) values for P_ET_CO_2_; cerebral oxygen monitoring values; blood pressure (systolic, diastolic, and mean); cardiac index, stroke volume variation, and cardiac performance index measured by the PULSION medical system (not mandatory); infusion rate of vasoactive drugs (dobutamine, ephedrine hydrochloride, noradrenaline, and other), and hourly urine output.Surgical data: type of surgery, duration of surgery, total volume of blood loss, surgical complications Y/N, and surgeon satisfaction.Intraoperative TEE monitoring data: intraoperative gas embolism grade, baseline for IVC-CI, and eccentricity index (EI) after anesthesia induction, and the grades and duration during gas embolism occurrence. EI is used to evaluate right ventricular volume and pressure overload [23]. IVC-CI and EI will also be recorded at the time of trocar insertion, the beginning of hepatic parenchymal transection, hepatic tumor removal, and following completion of the surgery. Vital signs, CVP, P_ET_CO_2_, cerebral oxygen monitoring values, ABG, and IVC-CI will also be recorded when any grade of gas embolism is detected by TEE.

After the surgical procedure, the following indices will be collected before hospital discharge:

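### The primary analysis ignores the three minimisation factors, which makes it conservative and forgoes some precision if those factors predict severe embolism

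*Protocol article*

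**What the plan says.** Under Randomization and blinding, the 1:1 sequence is "generated using a minimization algorithm stratified according to risk of intraoperative exposure of the hepatic vein, liver cirrhosis status, and history of abdominal surgery". Study visits and data collection confirms that the factors are captured as binary items when the patient is randomised: "risk of intraoperative exposure of hepatic vein Y/N, liver cirrhosis status Y/N, and history of abdominal surgery Y/N".

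Under Primary outcome, the treatment effect is to be "reported as numbers and percentages estimated with risk ratios and 95% confidence intervals (CI", followed by chi-square tests for the hypothesis. No covariate is named. The interval method is described by a phrase that joins Wald and likelihood-ratio terminology. The Sample size section rests on the same crude test: "126 participants are required to detect the observed difference in gas embolism incidence using chi-square test".

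The factors reappear only under Subgroup analyses, as factor-by-arm interactions in regression models. No adjusted primary or sensitivity analysis is described. Where Secondary outcomes does mention covariates, for 90-day mortality, it specifies a Cox model with none.

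**The concern.** Minimisation forces the arms to be alike on the chosen factors. If a factor predicts the outcome, this removes a source of chance difference between the arms. A crude chi-square test does not know that. Its standard error still includes the variation between factor levels, as if allocation had been simple. The result is a standard error that is too large, a true test size below 5% and an interval that is too wide.

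What is at stake is efficiency. The investigators have paid, through the allocation scheme, for precision that the primary analysis does not collect. The remedy has to be fixed before unblinded data are seen, because adjustment added later will look data-driven.

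**Working it through.** **Inputs from the protocol.** Event rates: "the incidence of grade 3 and above gas embolism in LLR using low and standard intra-abdominal pressure was 45% and 69%, respectively". Test: chi-square, at "a level of significance of 5% against the two-sided alternative hypothesis". Power 80%, drop-out 10%, ratio 1:1, three binary minimisation factors. The Analysis section excepts the primary outcome from two-sided 5% without giving an alternative. That is a separate matter. The calculations here use two-sided 5%, which is what reproduces the stated sample size.

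**Step 1: reproduce the stated figure.** Unpooled two-proportion formula, per arm:

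n = (1.960 + 0.842)² × (0.45×0.55 + 0.69×0.31) / (0.69 − 0.45)² = 7.85 × 0.4614 / 0.0576 = 62.87, so 63 per arm and 126 in total. Then 126 / 0.90 = 140. Both stated figures reproduce. (The pooled-variance version gives 66 per arm.)

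**Step 2: the mechanism.** Let p(x) be the event probability in stratum x. The variance that the crude test uses, p(1−p), splits into the mean of p(x)(1−p(x)) within strata plus the variance of p(x) between strata. Minimisation largely cancels the second part in the comparison of arms, and the crude test still counts it. If p(x) is the same in every stratum, the second part is zero and nothing is lost.

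**Step 3: size of the effect.** The protocol gives no odds ratios, factor prevalences or degree of randomness in the minimisation, so all three are assumptions. Simulation at 126 evaluable patients, with 45% versus 69% for power, assumed prevalences of 40/40/30% and a biased coin of 0.9:

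| Assumed odds ratios (vein / cirrhosis / surgery) | Size of crude test | Power, crude → modified Poisson | Gain, standardised logistic | Gain, Mantel-Haenszel |
|---|---|---|---|---|
| 2 / 1.5 / 1.5 | about 5% | 80.5% → 80.1% | about 0 | about −1 |
| 4 / 2 / 2 | about 4.4% | 80.5% → 82.5% | about 3 points | about 1 point |
| 6 / 2 / 2 | about 3.4% | 82.5% → 84.9% | about 4 points | about 3 points |

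The modified Poisson column comes from 3,000 trials per cell, with a Monte Carlo standard error of about 0.7 points for power.

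A separate simulation gave all three factors the same odds ratio. It used 126 patients, a null rate of 69%, two prevalence sets, coin 0.8 or 1.0, 4,000 trials per cell and an adjusted logistic score test:

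| Odds ratio per factor | Crude size | Adjusted size | Crude power | Adjusted power |
|---|---|---|---|---|
| 2 | 4.0–4.7% | 5.4–5.5% | 80–81% | 81–83% |
| 3 | 3.3–3.9% | 5.0–5.3% | 80–83% | 84–86% |
| 5 | 2.2–3.2% | 4.9–5.7% | 82–84% | 89–90% |

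At odds ratios of 1.0 and 1.5 the differences were within simulation noise.

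**Step 4: what this means for the interval.** A true size of 4.4% corresponds to a critical value of 2.014, and one of 3.4% to 2.120. Against 1.960 the crude standard error is too large by roughly 2.014/1.960 = 1.03 and 2.120/1.960 = 1.08. The interval is therefore about 3% and 8% too wide in those two scenarios (normal approximation, under the null).

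**The case against.** The strongest reply is that nothing is broken. The trial was sized for the very test it plans to use, and in every scenario above the crude test keeps about 80% power. Its error is in the safe direction. This stands. A reader might infer from the mismatch that the primary p-value is invalid, that its error bars are wrong in a way that threatens the conclusion, or that the trial is underpowered. The documents support none of these: there is no bias and no added false-positive risk.

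A second reply is that prognostic strength is assumed. This also stands. The Background says that hepatic vein rupture and sinusoid exposure enlarge the pressure gradient and raise embolisation risk, which gives a mechanism for the vein-exposure factor. Nothing in the document links cirrhosis or previous abdominal surgery to embolism. Choosing them for minimisation suggests that the investigators think they matter, but it is not evidence of how much.

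Third, larger gains can be produced. With 140 patients and a logistic likelihood-ratio test, power rises from 84.7% to 88.2% at 4/2/2 and from 84.7% to 89.8% at 6/2/2. Those figures ignore the expected drop-out. At 6/2/2 the adjusted test also has a size of 5.8%, so part of that gain is extra type I error.

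Fourth, an unseen analysis plan might add an adjusted sensitivity analysis. That would be reasonable, but here the article states the primary estimator and test outright, so this is a choice made and not a detail left open. The subgroup interaction models do use the factors, but they do not adjust the primary estimate.

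**Conclusion.** The point holds as a modest, conditional loss of efficiency. The mismatch between allocation and primary analysis is in the text, and the direction is certain if the factors are prognostic: the crude analysis is then conservative. At the planned 126 evaluable patients, adjustment is worth roughly 0 power points with weak factors (2/1.5/1.5), 1 to 3 with 4/2/2 and 2.5 to 4 with 6/2/2. These figures rest on assumed odds ratios, prevalences and coin bias, none of which the protocol supplies, so the size of the loss in this trial cannot be known from the document.

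Separately, the name given to the interval method merges two procedures, so the interval cannot be reproduced as written and need not agree with the chi-square p-value near the 5% boundary. This is a wording fault and does not make the adjustment point weightier, but the same change removes it.

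**What to change.** Make the primary analysis a model of severe embolism on arm plus the three minimisation factors: either logistic regression with marginal standardisation, or modified Poisson regression with robust standard errors. Name one of these in advance. Take the adjusted risk ratio, risk difference, 95% confidence interval and p-value from that single model, in place of the present description of the interval method. Keep the crude chi-square test as a supportive analysis, which preserves the link to the sample-size calculation.

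The cost is analysis wording only. The factors are already collected at randomisation, and 126 evaluable and 140 randomised patients can stand. There are two drawbacks. Adjusted tests can be slightly liberal at this sample size (up to 6.1% in one simulated cell with odds ratios of 1.5), so a small-sample variance correction should be specified. If the factors turn out to be weak, the gain will be negligible.
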